### Monitoring

The primary care center staff will be told to report any type of adverse event (for example, hospitalization, pregnancy, suicide attempt) affecting the participants to the principal investigator, who will then take appropriate measures to ensure the safety and wellbeing of the participants.

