Since 2001, Chile has had a program for the detection, diagnosis, and treatment of depression in primary care clinics. It recommends algorithms for diagnostic evaluation, delivery of psychosocial interventions and medications, consultations with specialists, follow-up visits, and criteria for referral to secondary care. All persons with depression have to be treated in primary care unless they have psychosis, bipolar disorder, high suicidal risk, or a lack of response to two courses of treatment with two different antidepressants at therapeutic doses, plus psychosocial intervention [10].

In 2006, depression was incorporated into the national health reform, thus ensuring universal access to treatment for depressed individuals 15 and older [11], the majority of whom are treated by primary care teams [12]. Since 2009, the Ministry of Health has published two Clinical Guidelines for depression treatment, but no training program has yet been recommended [10, 13].

An evaluation of the depression program carried out at seven primary care clinics in two regions of Chile demonstrated that diagnoses of the severity of illnesses were inaccurate, that severity of depressive episodes was underestimated, that treatments were not indicated according to the severity of the illness or according to guidelines, that adherence to treatment was insufficient − higher for pharmacological treatment and lower for individual psychotherapy and group psychoeducation − and that patient dropout from the program was around 60 % [14, 15].

International evidence indicates that, despite the high prevalence of depression and availability of effective treatments, the diagnosis and treatment of depression by general practitioners do not follow clinical guidelines and that these guidelines do not always include training [16, 17].

Training can improve the detection, diagnosis, and treatment and could lead to better patient outcomes, although studies have shown that training alone does not result in improved outcomes [18, 19].

There is abundant literature on the effectiveness of collaborative care on depression [20]. Systematic literature reviews of strategies employed to improve mental health patient outcomes reported that the most effective interventions incorporate clinician education, nurse case management, a greater integration between primary and secondary care [21], and quality measures to improve results [22].

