## Methods and design

This is a two-arm, single-blind (blinded only to outcome evaluator), cluster randomized controlled trial, which will compare the effectiveness of a comprehensive technology-assisted training and supervision program for depression management versus usual depression care in primary care clinics in Santiago, Chile.

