### Intervention arm

The intervention arm includes a 16-h training program for primary care teams (physicians, psychologists, social workers, nurses, midwives, and occupational therapists) to ensure compliance with the Clinical Guidelines for the Treatment of Depression, issued by the Chilean Ministry of Health [10]. The workshop will include a seminar on the detection, diagnosis, and treatment of depression; discussion of clinical cases; and role-playing to enhance clinical skills and to apply problem-solving techniques. Finally, trained primary care teams will undergo an Objective Structured Clinical Examination (OSCE) for evaluation.

After the training, a focus group between primary health care teams and study researchers will be held in order to address barriers to the implementation of clinical guidelines. In order to develop a comprehensive supervision program, trained administrative staff will contact patients from a call center to support treatment adherence, and a psychiatrists will supervise the primary care team, using a web-based platform.

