### Sample size

Sample size calculation was done based on two studies previously carried out in Chile [36, 15]. A randomized clinical trial that compared pharmacotherapy monitored by telephone with usual care in primary care clinics in Chile found a recovery rate for depressive disorders of 62 % in the intervention group versus 38 % in the control group [36], having an effect size of 20 %. Since the current study protocol aims to test whether the intervention is better than usual care, a one-sided test is appropriate to detect an effect. Moreover, it is expected that the intervention will have a favorable effect ruling out the possibility of a statistically significant negative effect. To detect a difference of 20 %, in a one-sided model, with an alpha of 5 % and power of 80 %, 152 depressed persons, 76 in each group (intervention and control), will be required for the study. Using a database from another study comprising 201 persons treated for depression in seven primary care clinics [15], an intraclass correlation coefficient (ICC) of 0.03839 was estimated. Therefore, a design effect of 2.42 was determined, based on the previously calculated ICC and the use of four clusters (primary care clinics). After applying the design effect, the sample needed increased to 368 depressed persons. Considering a retention rate of approximately 85 %, 434 depressed cases will be required for the study, hence 109 cases in each of the four primary health care clinics.

Finally, a group of four primary health care clinics was chosen for two reasons: the usual flow of patients with depression presenting at each of the participating primary care clinics, which allows for a high number of potential participants per clinic, and financial constraints restricted the number of clusters, since having more primary care clinics would put in jeopardy the feasibility of the study.

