### Data collection

All participants will be assessed at baseline and at 3 and 6 months after recruitment. Independent interviewers blind to treatment assignment evaluated participants at 3 and 6 months after baseline assessment. The interviewers received an 8-h training to ensure standardization of data collection, which will be performed using digital PDF forms. Interviewers and patients will use computer tablets for data entry.

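### The only stated adverse-event route is spontaneous reporting by unblinded clinic staff whose training and patient contact differ by arm, so events may be under-reported and counts by arm may not be comparable

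*Protocol article*

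**What the plan says.** The whole safety provision in the protocol article is the one sentence that makes up its Monitoring section: "The primary care center staff will be told to report any type of adverse event (for example, hospitalization, pregnancy, suicide attempt) affecting the participants". These reports go to the principal investigator, who then acts to protect the participants. No second source of events is named.

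Four other places bear on how this route will work.

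- **Blinding.** Methods and design describes the trial as "single-blind (blinded only to outcome evaluator"), so clinic staff know their arm.
- **Contact by arm.** Under Intervention arm, teams receive 16 hours of training, psychiatrists supervise them on a web platform, and "trained administrative staff will contact patients from a call center to support treatment adherence". Control arm describes usual care, with staff told to follow the national guideline. Hypotheses predicts better adherence and greater service use in the intervention arm.
- **Contact common to both arms.** Data collection says: "Independent interviewers blind to treatment assignment evaluated participants at 3 and 6 months after baseline assessment". Other outcomes adds that service use is measured at the same two times. Neither is tied to safety.
- **Loss from care and from the study.** Background reports, from an evaluation at seven clinics in two regions, that "patient dropout from the program was around 60" per cent. Sample size assumes about 85 % retention in this trial.

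**The concern.** A spontaneous report needs two things: the staff member must learn of the event, and must then pass it on. Both may depend on arm here. Intervention teams are trained and supervised in depression care, and their patients are called to keep them in treatment. If the trial's own hypotheses on adherence and service use are right, those teams also see their patients more often. The chance of hearing about a hospitalisation or suicide attempt is then tied to the effect that the intervention is meant to have.

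Two things are at stake. First, events in patients who have drifted out of the program, or who are managed by the specialised service after referral, may not come to the clinic's notice. That matters for participant safety even if the arms are never compared. Second, if events are tabulated by arm, as presentation under CONSORT makes plausible, a difference could reflect contact and not incidence. The likely direction is a higher count in the intervention arm, which could create a false excess there or hide a true excess in the control arm.

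**Working it through.** **The plan's own figures.** The article gives no adverse-event rate, capture rate or safety sample size, so there is no safety figure to reproduce. The 60 % dropout is cited without counts and cannot be recomputed. The retention figure is used consistently: 368 / 0.85 = 432.9, against 434 stated.

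**What the two loss figures measure.**

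| Figure | Measures | Source | Applied to 434 |
|---|---|---|---|
| about 60 % | dropout from the national depression program in a separate evaluation | Background | 434 × 0.60 = 260 |
| about 15 % | loss to assessment assumed for this trial | Sample size | 434 × 0.15 = 65 |

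These are different quantities. The first suggests that routine care may see many patients too rarely to be a good sole source. It is not a count of trial participants out of staff contact.

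**Effect of capture on a by-arm count.** Let *n* be the number per arm, *r* the true risk (equal in both arms), and *c*₁ and *c*₀ the capture proportions in the intervention and control arms. Expected reported events are *n·r·c*₁ and *n·r·c*₀, so the apparent risk ratio is *c*₁ / *c*₀, whatever the value of *r*.

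Inputs: *n* = 434 / 2 = 217 from the protocol. The values *r* = 5 % and *c*₀ = 40 %, and every value of *c*₁, are assumptions. True events per arm: 217 × 0.05 = 10.85.

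| *c*₀ | *c*₁ | Control reported | Intervention reported | Apparent ratio |
|---|---|---|---|---|
| 40 % | 40 % | 4.3 | 4.3 | 1.0 |
| 40 % | 60 % | 4.3 | 6.5 | 1.5 |
| 40 % | 80 % | 4.3 | 8.7 | 2.0 |
| 40 % | 100 % | 4.3 | 10.9 | 2.5 |

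Risks of 2 % and 10 % change the counts but not the ratios.

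**Under-counting without bias.** At 5 % risk there are 434 × 0.05 = 21.7 events in all. With 40 % capture in both arms the ratio stays at 1.0, but 21.7 × 0.60 = 13.0 events go unreported.

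**The alternative source.** If interviews reach 85 % in each arm, with full recall and disclosure and with loss unrelated to events, they find 10.85 × 0.85 = 9.2 events per arm and miss 21.7 × 0.15 = 3.3 in all. That is a best case, since a hospitalised participant may be more likely to miss the visit.

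**The case against.** The strongest reply is that this is a condensed article. Monitoring does not say that staff reports are the sole route, and event questions may sit in the full protocol. That limits the point to the route as stated. It does not remove it: the article fixes a method, passive and unblinded, while describing a better-balanced contact that it does not connect to safety. Service-use data may pick up some hospitalisations in both arms, but their source and content are not given and no safety use is stated.

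A second reply is that the route serves prompt action for participants, for which questions at 3 and 6 months come too late. This stands, and is why staff reporting should stay.

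A third is that no aim, outcome or analysis compares events by arm, that the reporting instruction is the same for both arms, and that call-center staff and supervisors are not named as reporters. All true. The comparison is plausible under CONSORT but not planned, and differential capture is a risk, not an established fact. The counts would also be too small to carry much weight: treating 6.5 and 4.3 as Poisson counts, the standard error of the log ratio is √(1/6.5 + 1/4.3) = 0.62, so a 95 % interval around 1.5 runs from about 0.4 to 5, before any allowance for four clusters.

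A reader might infer from the Background that staff will lose contact with about 260 of the 434 participants. The documents do not support this. The 60 % comes from another evaluation and concerns leaving the depression program, and someone who leaves the program may still attend the clinic.

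**Conclusion.** The concern holds as a risk built into the stated method. Adverse events reach the principal investigator through unblinded staff whose training and patient contact differ by arm by design, while blinded visits common to both arms are not used for this purpose. Events may be under-reported, and counts by arm may not be comparable.

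The size cannot be determined from the documents. With equal true risks, the distortion is exactly the ratio of capture rates: none with equal capture, 1.5 to 2.5 under the unequal splits tried. Those splits are assumptions, and the ratios only restate them.

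It would be tempting to conclude that serious events are missed and that any comparison of the arms is biased. The text supports only that this may happen. Equal capture would leave the ratio unbiased, and no by-arm safety analysis is specified.

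**What to change.** Keep prompt reporting by clinic staff as it stands, for participant safety. Add to Monitoring and Data collection that the existing 3- and 6-month interview form ends with a short fixed set of questions on hospitalisation, suicide attempt and pregnancy since the last visit. They are asked in the same words in both arms, after the PHQ-9 and the other outcome scales, and the answers are forwarded to the principal investigator. Base any by-arm safety table on these solicited answers, with the number interviewed in each arm as denominator, and list events known only from staff separately.

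The cost is about a minute per interview, a few items on a form already in use and a sentence or two in the protocol. There are four drawbacks:

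- Some recall error over three months.
- No solicited data from the roughly 15 % not retained.
- Remaining imbalance if retention differs by arm.
- A small chance that an answer reveals the arm. Placing the questions last protects the scales at that visit. It does not protect the 6-month visit if the same interviewer was unblinded at 3 months, although the PHQ-9 and OQ 45.2 are self-administered, which limits the effect.

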### Research governance and ethics

#### Trial management

The study will comply with local research governance requirements.

### Ethics

Full ethical approval was obtained from the local Ethics Committee (Faculty of Medicine, Universidad de Chile, project no. 103–2012). Informed and written consent will be obtained from the participants.

## Discussion

To date, only a single study in Latin America has evaluated changes in the knowledge, attitudes, and practice among primary care physicians who participated in a depression training program, finding limited impact on daily practice a month after the training program, measured through rates of diagnosis, referrals, antidepressant prescription, and provision of supportive therapy [39].

In contrast to the study mentioned above, our research protocol aims to evaluate the effectiveness of a training program in improving patients' outcomes and focuses not only on training primary care physicians in managing depression, but also the primary health care team as a whole in order to develop a comprehensive approach to depression management, which is further reinforced by a technology-assisted supervision program.

The aforementioned makes our study the first of its kind in a Latin American country. We believe that the training and supervision program can contribute to the Chilean national depression program, which is implemented in all the primary care clinics of the country despite primary care teams not currently being trained to follow the Ministry of Health recommendations for the correct detection, diagnosis, and treatment of depression [10].

### Trial status

The study started recruiting patients in June 2014. Recruitment will end by July 2015.

## Abbreviations

ICD-10: 10th revision of the International Statistical Classification of Diseases
PHQ-9: Patient health questionnaire-9-item
MINI: MINI Mini-International neuropsychiatric interview
OSCE: Objective structured clinical examination
SF-36: Short form-36 health survey
OQ45.2: Outcome questionnaire 45.2
ICC: Intraclass correlation coefficient
PDF: Portable document format
CSV: Comma-separated values
SPSS: Statistical Package for the Social Sciences
